#### Process evaluation

To identify programme factors that may influence the effectiveness of the standardised O&M-training and factors that may contribute to future improvement and implementation of the training a process evaluation is carried out. The main outcomes of the process evaluation are derived from previous work [52,53] and Saunders and colleagues [54] and include: population reached, performance according to protocol, exposure and engagement, opinion on the training, perceived benefit or achievement, and experienced barriers and potential solutions. Table 4 provides an overview of the outcomes of the process evaluation during the course of the trial. Data is collected from both the intervention group and the control group.

**Table 4 T4:** Outcome measures of the process evaluation

**Variable**	**Measurement**
**Population reached**	

Target population and proportion of the intended target population	TI-Rp, SQt
General characteristics of the participants and trainers	Qt
Number of participants that refused, dropped out or completed the training	Qt
Reasons for withdrawal	Qt

**Performance according to protocol**	

Format, preparation time and duration of the session	Qt
Per session component: extent to which carried out, duration and active participation by the participant*	Qt
Extent to which the trainer achieved to:	
- related to identification cane: provide information, raise the participant's awareness of its advantages, demonstrate the use and have the participant experience the use of the cane*	Qt
- have the participant phrase his/her important activities related to mobility and how to perform activities safely and independently*	Qt
- have the participant setting goals regarding an action plan*	Qt
- teach orientation skills* and teach mobility skills*	Qt

**Exposure and engagement**	

Total number of sessions	Qt
Use of materials*	TIp, Qt
Overall opinion of the trainer/participant regarding the participant's engagement in:	
- the training	TIp, Qt
- formulating of an action plan and carrying out an action plan*	Qt
Exposure and adherence to homework	TIp
Extent to which the participant complied with contracts*	Qt
Quality of actions plans formulated by the participants*	Qt

**Opinion on the training**	

Overall opinion on the training	TIp, Qt
Opinion regarding:	
- number, duration and course of the sessions	TIp, Qt
- homework and comprehensibility of the complete training	TIp
- number of extra training sessions needed	TIp, Qt
- whether the O&M-training met the participant's need for mobility support	TIp, Qt
Usefulness regarding:	
- discussing mobility problems, receiving information on different kinds of canes and practicing with the identification cane	TIp
- formulating an action plan and carrying out an action plan*	TIp
- contracting with respect to formulating and carrying out action plans*	Tip
Burden experienced by the participant	TIp
Recommendation of the training to others	TIp
Overall opinion on the trainer	TIp, Qt

**Perceived benefit or achievement**	

Benefit regarding:	
- the O&M-training	TIp
- advantages of an identification cane and self-confidence	Qt
- realistic action planning*	Qt
Use of identification cane in daily life	Qt
Achievement regarding:	
- identification cane: knowledge, aware of advantages and having experienced the cane	TIp
- able to think how to perform an activity safely and independently	TIp
- self-confidence and performance of an activity safely and independently	TIp
- formulating a realistic action plan* and carrying out an action plan*	TIp
- skills for orientation and skills for mobility	TIp
- safe and independent participation outdoors	TIp, Qt
- optimal use of personal capabilities	TIp, Qt
- starting new activities and/or taking up former activities that were avoided due to the mobility problems	TIp, Qt

**Experienced barriers and potential solutions**	

Deviations of each session component*	Qt
Main goal of contact - time spent on issues not related to O&M-training	Qt
Strong and weak aspects of the O&M-training	TIp, Qt
Hampering and stimulating factors for use of the standardised O&M-training*	Qt
Matters for improvement - materials and standardised O&M-training*	Qt

* Assessed in the intervention group only.

O&M-training = orientation and mobility training; TI-Rp = telephone interview prior to randomisation with the participant (as part of the screening process); SQt = starting questionnaire, i.e. questionnaire filled in by the trainer before training his/her first participant of the study; Qt = questionnaire filled in by the mobility trainer per participant; TIp = interview by telephone with the participant.

### Data collection

Data for the effect evaluation are collected at baseline, and at 5 and 17 weeks after the start of the O&M-training during 40-minute interviews by telephone. Trained interviewers, who are masked for group allocation, perform the interviews. In addition, a 25-minute interview by telephone is performed at 8 weeks after the start of the O&M-training to obtain data for the process evaluation from participants in the intervention group as well as the control group. Pre-structured questionnaires on process aspects are used to gather data from the mobility trainers per participant. Trainers receive this questionnaire before the first session of the participant's O&M-training. As recommended by Hollis and Campbell [55], non-compliant participants are approached for all follow-up assessments.

### Sample size and power

The power calculation is based on data from Kempen and colleagues [40] with regard to the primary outcome variable: GARS ADL self care. Two times 67 participants will provide 80% power at alpha .05 to detect differences between the intervention and control groups' mean change score of at least 3.5 points (SD is 8.1 equivalent with an effect size of .43 on the GARS ADL self care). However, a dropout during the study of 25% may be expected. Therefore, 2 × 95 participants are needed for randomisation.

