### Analysis

Data of the effect evaluation will be analysed according to intention-to-treat principle and on-treatment principle. Univariate techniques and mixed-effects regression analyses will be applied to test for between-group differences with respect to the primary and secondary outcome measures at all follow-up assessments. Models will be adjusted for relevant covariates, including age, gender and baseline differences. Descriptive techniques will be used to describe participants of the trial and to analyse the data of the process evaluation.

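### The 67 per group is reproduced only by an undeclared one-sided 5% test; read as two-sided it gives about 70% power, and 95 per group does not follow from 25% dropout

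*Protocol article*

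**What the plan says.** The protocol article, under Sample size and power, sizes the trial on one of its two primary outcomes, GARS ADL self care. It states that "Two times 67 participants will provide 80% power at alpha .05 to detect differences between the intervention and control groups' mean change score". The target difference is 3.5 points, and the spread is given as "SD is 8.1 equivalent with an effect size of .43 on the GARS ADL self care". It then says that "a dropout during the study of 25% may be expected" and concludes that 2 × 95 must be randomised. The abstract carries this forward as N = 190.

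The sidedness of the test is not given there. The Analysis section plans to "test for between-group differences with respect to the primary and secondary outcome measures at all follow-up assessments" and attaches no direction to the hypothesis. No baseline correlation, repeated-measures gain or other variance reduction is quoted as an input to the calculation.

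**The concern.** The calculation lists every input except the sidedness, so it can be checked both ways. A reader who meets an unlabelled alpha of .05 for detecting differences will assume a two-sided test. Under that assumption the stated number of completers falls well short of the stated power. The step from completers to recruits also does not follow from the dropout rate given in the sentence before it.

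The 80% is the article's only statement of how likely the trial is to detect the effect it names. If it is about ten points too high, a non-significant result will look more informative than it is. This matters here because, under Future implementation, the training may also be adopted when it is judged equally effective and more feasible.

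**Working it through.** **Inputs**, all from Sample size and power: difference 3.5 points; SD 8.1; alpha .05; power 80%; equal groups; dropout 25%. The standardised effect is 3.5/8.1 = 0.432, which agrees with the stated .43. Its square is 0.1867.

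**Reproducing the 67.** The normal-approximation formula is n per group = 2(z_alpha + z_beta)²/d², with z_beta = 0.842 for 80% power.

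- One-sided 5% (z_alpha = 1.645): 2 × (2.487)²/0.1867 = 66.2, so 67. The t-test calculation gives 66.9, also 67.
- Two-sided 5% (z_alpha = 1.960): 2 × (2.802)²/0.1867 = 84.1, so 85. The t-test calculation gives 85.05, so 86 if rounded up strictly.

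The article's figure is matched exactly by the one-sided test. It is 18 to 19 per group short of the two-sided requirement, which is too far for rounding to explain.

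**Power and detectable difference** (t-test, difference 3.5, SD 8.1):

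| Completers per group | One-sided 5% power | Two-sided 5% power | Difference detectable with 80% power, two-sided |
|---|---|---|---|
| 67 (as stated) | 80.0% | 69.9% | 3.95 points |
| 71 (95 less 25%) | 82.0% | 72.5% | 3.8 points |

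The normal approximation gives two-sided power of 70.6% and 73.1%, so the choice of method changes little.

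**Dropout step.**

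- Dividing by the retained fraction: 67/0.75 = 89.3, so 90 per group.
- Multiplying up, a common shortcut: 67 × 1.25 = 83.75, so 84 per group.
- Neither gives 95. Going from 95 to 67 means losing 1 − 67/95 = 29.5%.
- In the other direction, 95 × 0.75 = 71.25, so 71 completers per group.

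**Do the two discrepancies cancel?** No. The extra recruits raise the completers from 67 to 71, which lifts two-sided power only from 69.9% to 72.5%. For scale only, 85 to 86 completers with 25% dropout would correspond to 85/0.75 = 113.3 or 86/0.75 = 114.7, that is 114 to 115 recruits per group.

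**The case against.** The strongest reply is that the article never says two-sided. With a one-sided 5% test, the 67 is exactly right, and the first half of the point is then an undeclared assumption rather than an arithmetic error. This stands, and it is why the power shortfall is stated here as conditional. It does not remove the point. Nothing in the article declares a one-sided test, and the choice changes the required number by about a quarter of the existing size (85 or 86 against 67). One might add that a condensed article may leave sidedness to the full protocol. The difficulty is not an omitted detail, however: the article prints a size, a power and an effect that do not agree under the reading its own wording invites.

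A second reply is that covariate adjustment could justify 67 with a two-sided test. That would need the SD of 8.1 to shrink by a factor of √(1 − r²) with r about 0.46, since 1 − 67/85.05 = 0.212 and √0.212 = 0.46. No such correlation is given, and the calculation is framed on the change score.

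A third reply is that the dropout slip is harmless. It is conservative: 95 exceeds the 90 needed, and on the one-sided reading the 71 completers give 82% power. It is an inconsistency to correct, not a cause of low power.

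A fourth is that the target is already moot, because Progress of the study concedes that 2 × 95 will not be enrolled. That disclosure counts in the authors' favour and limits what the correction can change. The same passage still refers back to the power calculation as the benchmark, so the benchmark should be right.

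Two stronger readings are tempting. A reader might infer that the trial as sized has a 30% chance of missing its target effect. That is the figure at 67 completers; at the planned 95 less 25% it is about 27% (1 − 0.725 = 0.275), and only if the test is two-sided. A reader might also take the rule under Future implementation, which separates more effective from equally effective, as proof that a two-sided test was meant. It is not: the rule attaches no separate action to a worse result and fits a one-sided question at least as well.

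**Conclusion.** The point holds in conditional form. The 67 per group is the one-sided 5% number, and no one-sided test is declared. Under the conventional two-sided reading, power for 3.5 points is about 70% at 67 completers per group and about 72.5% at the 71 that the recruitment target would leave, against a stated 80%; 80% would need 85 to 86 completers per group. Whichever sidedness was meant, 95 does not follow from 67 and 25% dropout, though that error is on the safe side.

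These results rest on the article's own difference and SD, equal groups, an unadjusted comparison of mean change, and independent participants. The last of these is favourable to the plan, because local centres were randomised, and any positive correlation within centres would lower power further. Achieved power will be lower again because enrolment will stop short of 2 × 95. The documents do not support saying that the calculation is wrong outright, because the sidedness is simply not stated.

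**What to change.** Amend the Sample size and power paragraph as follows.

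1. State whether the 5% test is one- or two-sided. If it is one-sided, say so there and in Analysis; the 67 then stands.
2. If it is two-sided, replace the claim of 80% power for 3.5 points. Either give the power as about 70% at 67 and about 72.5% at 71 completers per group, or keep 80% and give the detectable difference as about 3.95 points at 67 and about 3.8 points at 71.
3. Make the dropout step consistent: 67 completers lead to 90 recruits per group, or 95 recruits lead to 71 completers per group. If a loss of about 29.5% was intended, state that rate instead of 25%.
4. Add one sentence saying that these figures precede any allowance for randomisation by centre and that, as Progress of the study already reports, 2 × 95 will not be reached, so achieved power will be lower.

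The cost is one corrected paragraph and, if the test is two-sided, a stated power about ten points lower. No added enrolment and no change to the design is proposed.

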### Analysis

Data of the effect evaluation will be analysed according to intention-to-treat principle and on-treatment principle. Univariate techniques and mixed-effects regression analyses will be applied to test for between-group differences with respect to the primary and secondary outcome measures at all follow-up assessments. Models will be adjusted for relevant covariates, including age, gender and baseline differences. Descriptive techniques will be used to describe participants of the trial and to analyse the data of the process evaluation.

## Discussion

O&M-training is a common health care service provided by organisations for rehabilitation care for people with visual impairment. The training aims to maintain independence of travel by teaching visually impaired persons to ambulate and negotiate the environment safely and independently. It may decrease mobility limitations and contribute positively to societal participation and quality of life. In an ageing population it is important to positively influence these domains to prevent physical, mental and social dysfunctioning which can lead to disability and institutionalisation. Yet, evidence on the effects of O&M-training in older adults with visual impairment is scarce, particularly with respect to the O&M-training in the use of an identification cane. This paper presents the design of a randomised controlled trial that will evaluate the effects and feasibility of a standardised O&M-training in the use of the identification cane by older adults with low vision in The Netherlands.

### Progress of the study

The screening procedure for eligible participants started in November 2007 and will continue until October 2009. In April 2009 28 participants (14 control group, 14 intervention group) had completed the training and follow-up assessments and another 11 participants (7 control group and 4 intervention group) had finished the O&M-training and the follow-up assessment at 5 weeks.

Recruitment of the participants by the collaborating organisations Bartiméus and VisioSensisDeBrink Group is slower than expected based on a dossier study by Verstraten and colleagues [56] and information obtained by the first author during interviews with mobility trainers. Reasons for the slow recruitment of participants as stated by the organisations include, among others, lack of eligible clients, lack of interest of clients to participate in the study, other research studies target the same population, work load of the mobility trainers and employees who perform the screening, unwillingness of mobility trainers to wait for the necessary research actions – such as obtaining informed consent and performing an baseline interview – before starting the training, adoption of new computerization system, etc. Although numerous actions have been undertaken to facilitate the organisations in the process of screening and to limit the time for research actions, recruitment of sufficient participants remains the main challenge of this study. The financial budget for the study allows to screen for eligible participants until October 2009. The 2 × 95 participants based on the power calculation will not be enrolled at that time.

Detailed information regarding the development of the standardised O&M-training and the effect and process evaluation will be presented in forthcoming papers. Preliminary findings regarding the evaluation are expected in the course of 2010.

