**Methods/design:**

A parallel group randomised controlled trial was designed to compare the standardised O&M-training with usual care, i.e. the O&M-training commonly provided by the mobility trainer. Community-dwelling older people who ask for support at a rehabilitation centre for people with visual impairment and who are likely to receive an O&M-training in using the identification cane are included in the trial (N = 190). The primary outcomes of the effect evaluation are ADL self care and visual functioning with respect to distance activities and mobility. Secondary outcomes include quality of life, feelings of anxiety, symptoms of depression, fear of falling, and falls history. Data for the effect evaluation are collected by means of telephone interviews at baseline, and at 5 and 17 weeks after the start of the O&M-training. In addition to an effect evaluation, a process evaluation to study the feasibility of the O&M-training is carried out.

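### The abstract's N = 190 and the 80% power statement are not reconciled with the admitted recruitment shortfall, which leaves the equal-effectiveness route to adoption exposed

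*Protocol article*

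**What the plan says.** The abstract (Methods/design) describes the participants as community-dwelling older people who ask a rehabilitation centre for support and are "likely to receive an O&M-training in using the identification cane are included in the trial (N = 190").

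Sample size and power states: "Two times 67 participants will provide 80% power at alpha .05", for a difference in "mean change score of at least 3.5 points (SD is 8.1 equivalent with an effect size of .43 on the GARS ADL self care"). It adds that "a dropout during the study of 25% may be expected" and concludes: "Therefore, 2 × 95 participants are needed for randomisation".

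Progress of the study reports: "In April 2009 28 participants (14 control group, 14 intervention group) had completed the training and follow-up assessments". Another 11 clients (7 control, 4 intervention) had reached the 5-week assessment. The budget allows screening only until October 2009, and: "The 2 × 95 participants based on the power calculation will not be enrolled at that time". The section gives no count of clients enrolled and no number expected at the stop.

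The abstract's Discussion paragraph and the Future implementation section set the rule for using the result. The standardised training enters the national instruction for mobility trainers if it proves more effective, or if it is equally effective and judged more feasible. The abstract gives the October 2009 stop but not the shortfall.

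**The concern.** The article states a size and a power, and then says that the size will not be reached. A reader of the abstract alone, or of the abstract and the power section, is told of a trial of 190 with 80% power. The only correction is one sentence in the Discussion, without numbers.

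This bears on the adoption rule. Its second branch is triggered by equality, and the article does not say how equality will be judged. A small trial will often give a non-significant difference whether or not the trainings differ by the 3.5 points it was designed to detect. If non-significance is taken as equality, national practice could change on feasibility alone, on evidence that leaves the design difference open.

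**Working it through.** **Inputs from the article.** Difference 3.5 points, SD 8.1, alpha .05 with sidedness not stated, power 80%, dropout 25%, 2 × 67 evaluable, 2 × 95 randomised. Screening runs from November 2007 to October 2009, taken as 23 to 24 months. Clients at or past the 5-week interview in April 2009: 28 + 11 = 39.

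**Assumed, because the article does not say.** Constant accrual; 17 to 18 months elapsed by April 2009; a lag of 0 to 4 months between screening and the 5-week interview; early loss of 0% to 25% before that interview.

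**1. The plan's own figure.** n per group = 2 × (z_alpha + z_power)² × (SD/difference)².
- One-sided: 2 × (1.645 + 0.842)² × (8.1/3.5)² = 66.2, so 67, as stated.
- Two-sided: 2 × (1.960 + 0.842)² × (8.1/3.5)² = 84.1, so 85.

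The stated 67 therefore corresponds to a one-sided alpha of .05, and both versions are shown below. The 95 does not follow from 67 and 25% dropout, since 67/0.75 = 89.3, so 90. Both are separate matters and are not pursued here.

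**2. Projection to October 2009.** N = count / months elapsed × total months.
- 39 clients, no lag: 39/18 × 23 = 50 to 39/17 × 24 = 55.
- 39 clients, lag of 2 to 4 months: 39/16 × 23 = 56 to 39/14 × 24 = 67.
- 39 taken as net of 25% loss (39/0.75 = 52 started): 52/18 × 23 = 66 to 52/14 × 24 = 89.

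The overall range is about 50 to 89, which is 26% to 47% of 190. Counted as evaluable clients, 50 to 67 is 37% to 50% of the 134 required. For comparison, reaching 190 would need (190 − 39)/6 = 25 new clients a month from April to October, or (190 − 52)/6 = 23 if 52 had started, against 39/17 = 2.3 a month so far.

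**3. Power and precision at those sizes.** Two-sample t-test, effect size 3.5/8.1 = 0.432, every projected client counted as evaluable, clustering ignored. Half-width of the 95% interval = t(0.975) × 8.1 × √(2/n).

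| Per group (total) | Power, two-sided | Power, one-sided | Half-width, points |
|---|---|---|---|
| 25 (50) | 32% | 45% | 4.6 |
| 29 (58) | 37% | 49% | 4.3 |
| 38 (76) | 46% | 59% | 3.7 |
| 44.5 (89) | 52% | 65% | 3.4 |

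At 29 per group, 80% power needs a true difference of about 6.1 points two-sided or 5.4 one-sided. At 44.5 per group it still needs about 4.9 or 4.3.

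The last row is an upper bound. The 89 arises only if a quarter of starters are lost. Deducting that 25% leaves about 33 per group and power of about 41% two-sided or 54% one-sided.

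**4. What an interval could exclude.** With an observed difference of exactly zero, the interval runs to ±4.3 points at 29 per group and ±3.7 at 38. Neither excludes 3.5. At 44.5 per group it reaches ±3.4 and only just does. At that size, any observed difference above about 0.1 points in favour of the training leaves 3.5 inside the interval.

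**5. Other influences.** Randomisation is by local centre (18 centres), which lowers power somewhat. With an assumed intraclass correlation of 0.01 to 0.10, N = 63 and 25% dropout, the normal approximation gives 43% to 40% one-sided and 31% to 28% two-sided, against 44% and 32% without clustering. The planned covariate-adjusted mixed models could recover some power, but the article gives no correlation from which to say how much.

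**The case against.** The strongest reply is that nothing is hidden. Progress of the study admits the shortfall and gives counts by group, reasons and the budget limit. That stands, and it rules out reading the article as presenting 190 as attainable throughout.

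A second reply is that the sample size section is a design calculation. It says what is needed, not what will be enrolled, and missing a target does not falsify it. This is fair for that section. It does not cover the abstract, which words 190 as the number included, and it does not help a reader judge what the trial can show.

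Third, a reader might infer that the trial will recruit about a third of its target. The article does not establish this. The 39 are clients who reached an interview, whereas the 190 is a number to randomise before dropout. Only a range under stated assumptions is defensible.

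Fourth, a reader might infer that the trial will more often than not miss the design difference. Two-sided, that is so at 29 and 38 per group but not at the most favourable projection (52%). One-sided, which is the version that reproduces the 67, power is 49% at 29 per group and 59% at 38, so the statement does not hold generally.

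Fifth, low power does not license a false claim of superiority; it makes such a claim harder to reach. The exposed branch is the one on equality.

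Finally, reporting conventions usually belong to the analysis plan or the results paper, and the results paper may well state its actual size. But the adoption rule is in this article, so its wording can be settled here.

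**Conclusion.** The point holds in limited form. The abstract's N and the stated power are not reconciled with the article's own admission that the 2 × 95 will not be enrolled. No projection from the reported counts restores 80% power for 3.5 points, one-sided or two-sided. The best case is about 65% or 52%, and a mid-range case of 29 per group gives about 49% or 37%. These figures rest on constant accrual, the assumed lag and dropout, every projected client being evaluable, an unadjusted comparison and no clustering. Further dropout or clustering would lower them; covariate adjustment might raise them by an unknown amount.

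The practical consequence lies in the equal-effectiveness branch. At 29 to 38 per group, an interval centred on zero would still contain the design difference, so a non-significant result would not by itself show equality. The documents do not support a charge of concealment, a fixed final size, or a bias towards finding the training more effective.

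**What to change.** - Abstract: label 190 as the original target and give the number expected at the October 2009 stop as a range, from the actual enrolment count if the sponsor has it.
- Sample size and power: keep the design calculation. Beside it, state the power for 3.5 points and the difference detectable with 80% power across that range, with the sidedness used.
- Abstract (Discussion) and Future implementation: state that a non-significant difference will not by itself count as equal effectiveness, and that the judgement will rest on the estimated difference and its confidence interval.

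The cost is text only, with no extra clients or budget. The downside is that the stated power becomes less favourable and the equality branch becomes harder to satisfy.
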